### Evaluation of the implementation

Experiences from each interview midway through the periods of implementation will be analyzed in an overall analysis based on the Model of Knowledge to Action Cycle [22]. This analysis will be supplied by focus group interviews with the ITASPA committee chairpersons at the end of the intervention period.

### Ethical considerations

The implementation of the project within worksites depends on the consent of the top management. At learning workshops, worksites will be encouraged to share experiences with their work environment initiatives. During this process, company-sensitive information may be shared. Thus, in workshops, it will be pointed out that a duty of confidentiality is expected among companies.

Personal information will be obtained from the participants about safety at work, workability, MSD, and psychosocial well-being. Data will be stored and processed as prescribed by the Danish Data Protection Agency and will only be available to researchers involved in this study. Data will be anonymized in analyses and feedback to the worksite will be provided anonymously, and in groups of at least 10 participants. The ITASPA facilitators will discuss any unforeseen ethical aspects with the worksites if they experience any. In this context, the steering group and reference group will be involved as potential sparring partners.

## Discussion

The aim of the ITASPA project is to investigate the effects and implementation of the Australian WIN program adapted to the Danish context. The background, design, intervention methodologies, and evaluation methods have been described. Effective interventions aiming to reduce work-related MSDs and mental disorders remain to be established, and to this date only a few integrated worksite intervention studies have been conducted in a Danish context [23–25].

### Impacts of results

We hypothesize that an integrated approach will improve the health and wellbeing of workers and strengthen the occupational safety culture. Other international experiences show that comprehensive, integrated worker health programs linking health protection and health promotion activities increase overall health and safety at worksites more effectively and rapidly than more narrowly focused programs [6, 14]. For example, changes aimed at sleep deprivation as a safety issue have also shown improvements on health issues such as diabetes, obesity, and cardiovascular disease among workers [26]. Therefore, integrated approaches can create health improving changes that lies beyond what is traditionally categorized as occupational health and illness [6]. Thus, implementing an integrated worksite intervention in a Danish context has potential to address important public health issues by using the worksite as arena.

In ITASPA, activities are integrated and adapted into existing core tasks, health promotion/disease prevention strategies, and organizational structures at the worksite. Hence, initiatives developed in ITASPA can be integrated across organizational structures. Furthermore, ITASPA involves employees and managers in the development and implementation of initiatives. Such a participatory approach in interventions for workplace improvements has previously shown to effectively improve health conditions such as mental health [27]. However, earlier worksite interventions have lacked implementation and comprehensive evaluation. As ITASPA will evaluate the effect and process of an integrated worksite intervention in a strong scientific mixed-methods design, ITASPA will provide knowledge about the barriers and facilitating factors for the implementation. Thus, ITASPA has the potential to contribute to the knowledge about what characterizes a best practice for the implementation of integrated worksite interventions in a Danish context.

### Strengths and limitations

Even though RCTs are the golden standard for intervention studies, it is not always practically possible, nor feasible, to have a control group of employees working at worksites that will not be affected by the intervention. However, the stepped wedged design will function as an RCT as it allows for comparison of control and intervention effects within the same environment, without increasing the risk of contamination between the intervention and control group, which reduces the risk of bias. Moreover, a stepped wedge design can prevent ethical objections arising from withholding an intervention anticipated to be beneficial [28]. In addition, a stepped wedge design will overcome issues with impaired organizational commitment and disappointed participants in the control group since all participants will be offered the intervention, and thus increases the participants’ obligations to the project [25]. Yet, the stepped wedge design still allows a sound scientific evaluation in a RCT design and address important ethical considerations, thereby increasing the possibility of a high number of participants and compliance, leading to stronger estimates in our data analysis.

Some limitations of the intervention design also deserve to be mentioned. As all employees will receive the intervention, it is not possible to blind participants or those involved in delivering the intervention. Hence, information bias may appear, particularly when outcomes are subjective. E.g. it is possible that participants are likely to report more positive health outcomes due to extended awareness of changes in these conditions after having received the intervention, leading to stronger effect-estimates of the intervention [28].

Furthermore, selection bias may challenge the generalizability of the results: it is plausible that healthy workers are more likely to stay at work longer than those who are injured or made sick from work [29] (healthy worker selection bias). This may reduce the potential to identify adverse health effects from work, leading to weaker estimates of the effect of risk factors on the health outcomes. However, by using a screening questionnaire we can examine if those who want to participate are different from those who do not want to participate.

The companies are randomly sampled, allowing for enrollment of diverse industries. Thus, we are able to investigate if the integrated approach can be translated and be successful in different lines of industries. Previous findings from worksite intervention studies show that the beneficial effects of an integrated worksite intervention are seen across different industries such as cleaning services [30], healthcare [16], construction, and manufacturing [23]. Moreover, worksite intervention studies have shown significant beneficial changes among employees in different countries [14]. These results suggest that integrated approaches in worksite intervention programs can be relevant and implemented in diverse industries and countries.

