**Methods:**

Using a stepped wedge design, worksites will be enrolled at baseline and offered the intervention starting at different times. Data will be collected at baseline, before the off-set of the intervention, and after each implementation period. The effect evaluation will be based on a mixed-methods approach. The qualitative data are based on semi-structured interviews and focus groups. The quantitative data consists of questionnaires, anthropometrics, and resting blood pressure and will be analyzed based on the intention-to-treat principle in linear mixed models with random slope and intercept.

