## Methods

### Study design

ITASPA is a worksite intervention, conducted in a stepped wedge design (Fig. 1) [16]. The stepped wedge design are assumed to increase the willingness to participate as it allows all workers to receive the intervention. The workers function as their own control and thereby, the stepped wedge design allows for an effect-evaluation, mimicking an RCT design.

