### Recruitment

To increase the transferring of the WIN program to a broad variety of Danish worksites, both public and private worksites are aimed to be enrolled. The worksites will be enrolled on basis of their willingness to perform the ITASPA activities during paid worktime and participation in the scientific evaluation of the ITASPA project. Workers will be included in the scientific evaluation of the ITASPA project by the following criteria: aged 18 – 67 years old at baseline; employed at one of the enrolled worksites ≥ 20 h/week; not being pregnant; ability to understand and speak Danish or English; providing an informed signed consent prior to participation.

An information meeting at the worksites will be held before initiating the intervention. At the meeting, the background and aim of the ITASPA project are introduced. All workers will be invited to fill out a screening questionnaire in which they can choose to sign up for participation in the scientific evaluation.

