### Effect evaluation and analyses

The effect evaluation will be based on a mixed-methods approach, where questionnaire data on MSDs, psychosocial wellbeing, safety culture, and workability will be measured based on the questionnaire-based interviews. The quantitative data will be analyzed based on the intention-to-treat principle in linear mixed models with random slope and intercept. The repetitive measurements within and between participants will be accounted for by nesting participants in clusters at the worksite level. The intervention will be included as a categorical variable with two levels, comparing the intervention period with the control period as a fixed effect in the model. Intercorrelation of repeated measurements will be included in the models as a random effect. Participants missing data on exposure or outcome variables will be excluded from analyses. All analyses will be conducted in SAS version 9.4 and/or SPSS version 27.0.

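### The article calls its companies randomly sampled although they are enrolled on willingness, and it rests its RCT claims on features that do not make a stepped wedge a randomised trial

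*Protocol article*

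**What the plan says.** On how worksites enter the study, the Protocol article says two things. Recruitment: "The worksites will be enrolled on basis of their willingness to perform the ITASPA activities during paid worktime", together with willingness to take part in the evaluation. Strengths and limitations: "The companies are randomly sampled, allowing for enrollment of diverse industries". Ethical considerations adds that implementation depends on top management's consent.

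On allocation, the Abstract (Methods) says "worksites will be enrolled at baseline and offered the intervention starting at different times", and Study design says "ITASPA is a worksite intervention, conducted in a stepped wedge design". Neither states how a worksite gets its start time.

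On validity, three statements increase in strength:
- Study design: "the stepped wedge design allows for an effect-evaluation, mimicking an RCT design". The ground given is that workers are their own controls.
- Strengths and limitations: "the stepped wedged design will function as an RCT as it allows for comparison of control and intervention effects within the same environment".
- Strengths and limitations, later: "the stepped wedge design still allows a sound scientific evaluation in a RCT design".

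Apart from the sampling sentence, the word random is used only for model terms (random slope, intercept and effect).

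**The concern.** The two claims concern different things. Random sampling of companies bears on how far the results generalise. Random allocation of start order bears on whether the effect estimate is causal. The first could not support the second even if it were true.

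If the sampling sentence stands, readers may take the results to represent companies at large, when the worksites are those willing to give paid work time to the programme. Willing worksites may also be those best able to carry it out.

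If the RCT wording stands and the order was not in fact randomised, start time could be tied to a worksite's readiness or to its current level of complaints. Recovery from a temporary peak would then be credited to the intervention, and the report would present that as randomised evidence.

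**Working it through.** The point is mainly one of wording and design. The only design figure in the article is the cluster size of 65 in Power calculation. It cannot be reproduced because no effect size is given, and this point does not depend on it.

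**Step 1: sampling.** Recruitment gives a rule (willingness) and no sampling frame or random draw. The Discussion asserts random sampling. The most generous reconciliation is that companies were approached at random and the willing ones enrolled. The article does not say so, and the enrolled set would still be self-selected. The selection-bias paragraph in Strengths and limitations covers workers (healthy-worker selection, participants against non-participants) and does not mention volunteering by worksites.

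**Step 2: RCT status.** The article offers two grounds.
- *Own controls.* Any before-after study has this.
- *Same environment.* Any before-after study at one worksite has this too.

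Neither protects against a start time that is related to the worksite's state or to calendar time. Random ordering of the starts does, and no such statement appears.

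**Step 3: a worst-case illustration.** Every input except the cluster size (65), the five measurements and the variance (2.1) is an assumption.
- Four worksites. Worksite k starts after measurement k (k = 1 to 4), so it has k control and 5 - k intervention measurements, giving 10 control and 10 intervention cells in all.
- No true effect. The mean score is 0 except for a temporary rise of 0.3 at each worksite's last control measurement. Higher scores are taken as worse.

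The ends of the range can be worked by hand.

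*Without period effects*
- No correlation: intervention mean 0, control mean 4 x 0.3 / 10 = 0.12, so the estimate is **-0.12**.
- Comparison wholly within worksite: each worksite's difference is -0.3/k with weight k(5 - k)/5. The weighted sum is -0.3 x (4 + 3 + 2 + 1)/5 = -0.6, the weights sum to (4 + 6 + 6 + 4)/5 = 4, and -0.6/4 = **-0.15**.

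*With period effects*
- No correlation: the proportion p of worksites on intervention at the five measurements is 0, 0.25, 0.5, 0.75, 1. The numerator is -0.3 x (0 + 0.25 + 0.5 + 0.75) = -0.45. The denominator is 4 x sum of p(1 - p) = 4 x 0.625 = 2.5. The estimate is **-0.18**.
- Within worksite: after removing worksite and period means, the intervention indicator at worksite k's last control measurement is -(5 - k)/5 - (k - 1)/4 + 0.5 = -0.25 - 0.05k, which sums to -1.5 over the four worksites. The residual sum of squares is the sum over intervention cells (worksite k, measurement t) of 0.5 + k/5 - (t - 1)/4 = 5 + 4 - 7.5 = 1.5. The estimate is 0.3 x (-1.5)/1.5 = **-0.30**.

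Generalised least squares with ICC 0 to 0.10 and within-person correlation 0 to 0.7 stays between these ends: about -0.18 to -0.30 with period effects (SE about 0.08 to 0.14 at variance 2.1) and -0.12 to -0.15 without. The model in Effect evaluation and analyses is described as "comparing the intervention period with the control period as a fixed effect in the model" and names no period term, so both cases are shown.

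**The case against.** The strongest objection is that the allocation limb leans on silence. This is a condensed article, I had only the caption of Fig. 1, and a full protocol may describe a random start order. That stands. A reader might infer that the order was not randomised, or that worksites or the team chose the starts. The document supports neither inference. What remains is that the article itself explains why the design is RCT-like, and the explanation it gives is not a valid reason.

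Second, the verbs used for mimicking and functioning as an RCT are partly analogies, and the same section concedes that RCTs are not always feasible. This is fair for those two sentences. The third ("the stepped wedge design still allows a sound scientific evaluation in a RCT design") is literal, and would be defensible only if the order was in fact randomised.

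Third, the sampling sentence occurs once, in the Discussion. No analysis uses it, and its stated purpose is diversity of industries, with transferability argued mainly from earlier studies. That limits its reach. It does not remove the conflict with Recruitment.

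Fourth, the illustration has every worksite starting at a temporary peak that vanishes by the next measurement. It is a worst case and not a prediction. It also cannot be expressed as a share of the planned effect, because the article states no effect size.

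**Conclusion.** The point holds as a matter of what the article asserts. The sampling claim conflicts with the recruitment rule: the worksites are volunteers on any reading. The RCT claims are not supported by the reasons given for them. Whether the start order was randomised cannot be settled from this document.

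The size of any bias is unknown. Under the stated worst-case assumptions it is about -0.18 to -0.30 points with period effects and -0.12 to -0.15 without, in the direction of false benefit. The effect of worksite volunteering on generalisability cannot be quantified from the article. The conclusion does not rest on these figures. The correction matters because the wording governs both the causal claim and the population to which the results may be applied.

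**What to change.** 1. **Sampling.** Replace the random-sampling sentence with a statement that worksites were recruited on willingness. Add worksite volunteering to the selection-bias limitations and limit generalisation to willing worksites. This costs only wording.
2. **Start order.** If it was randomised, say so, giving the unit, method and concealment. If any starts are still open, randomise those. The cost is one allocation list, and worksites can no longer choose their start. With few worksites or starts left, there may be little to randomise.
3. **Otherwise**, delete the RCT wording in Study design and in Strengths and limitations, and report a non-randomised staggered-start study. The cost is a weaker causal claim.
4. Label any bias illustration as a worst-case assumption and give it as a range.

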## Data Availability

The datasets that will be used and/or analyzed during the current study are available from the corresponding author on reasonable request.

## Abbreviations

ITASPA: Integrated Approach to Health, Wellbeing, and Productivity at Work
WIN: WorkHealth Improvement Network
TWH: Total Worker Health
MSDs: Musculoskeletal Disorders
WORQ: Work Rehabilitation Questionnaire
NOSACQ-50: Nordic Occupational Safety Climate Questionnaire
BMI: Body Mass Index
PDSA: Plan-Do-Study-Act
